## Sample size calculations

The sample size and calculated power for the primary outcome of negative cultures for *Candida albicans* is based on data in Alvendal et al. Acta Obstet Gynecol Scand. 2017. In that study there was 100% positive cultures for *Candida albicans* before routine treatment with fluconazole for RVVC. After fluconazole treatment, 14% participants were still culture positive, with 86% success rate of primary outcome. Using the presumption: α= 5% β= 90%, success for routine FLZ treatment= 86%, success for experimental treatment with CHG in the current study= 86% with non-inferiority limit= 30%, 46 participants are needed (23 in each group) to achieve a power of 90 % not to exclude an effect-size of 30%. 60 participants will be included in case of drop-outs. All test will be performed at the 5% significance level.

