# Synopsis

The overall aim of this study is to investigate if vaginally applied 1% chlorhexidine gluconate (CHG) could be an alternative treatment to oral fluconazole (FLZ), both during an acute episode and as prophylaxis, against recurrent infections of vulvovaginal candidiasis (RVVC). If CHG is at least as effective as FLZ with little impact on vaginal lactobacillus, with high tolerability and without cytotoxic effect on epithelial cells, the results of the study might lead to major benefits to the patients with reduced risk of systemic side effects such as drug interactions, development of drug resistance and reduced drug costs.

| EudraCT number:  2020-000758-81 |  |
| --- | --- |
| Title: A RCT for chlorhexidine gluconate as treatment and prophylaxis for Recurrent Vulvovaginal Candidiasis |  |
| Study code: Chlorhex-KKDS-2021 |  |
| Short background/ Rationale/Aim:  Recurrent vulvovaginal candidiasis is common in young fertile women. There are limited treatment options and the recommended treatment of long-term oral fluconazole is not suitable for all patients. The overall aim of this study is to investigate if vaginally applied 1% chlorhexidine gluconate (CHG) is at least as effective as oral fluconazole, both during an acute episode and as prophylactic treatment for recurrent vulvovaginal candidiasis (RVVC). |  |
| Study objectives:  RCT to compare the treatment effect and  safety aspects of vaginal 1%chlorhexidine  gluconate (Hibitane® vaginal cream)  versus oral fluconazole (Fluconazole®)  for recurrent vulvovaginal candidiasis  (RVVC). | Primary objective:  To analyze if vaginal application of CHG is at least as effective as oral FLZ as treatment and prophylaxis of RVVC in terms of clearing the infection (negative culture for *Candida albicans*)  Secondary objectives:  To analyze adverse events  To analyzed clinical symptoms and findings  To study the event of relapses during and after the prophylaxis treatment  To study the effect on vaginal microbiome of lactobacillus before and after treatment and prophylaxis with CHG for RVVC.  To investigate if CHG have toxic effect on the vaginal epithelial cells.  To analyze vaginal biofilm formation before and after treatment and prophylaxis with CHG for RVVC. |
| Study design:  The study is a randomized open Phase II trial and the protocol is designed as a non-inferiority trial. |  |
| Study population:  Women with culture verified recurrent vulvovaginal *Candida albicans* infection |  |

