## Statistical analyses

### Statistical methods

***Objective:*** The aim of this study is to analyze whether vaginal chlorhexidine gluconate (CHG) is at least as effective and safe as oral fluconazole (FLZ) as treatment and prophylaxis for recurrent vulvovaginal candidiasis.

***Study design:*** Randomized controlled non-inferior trial with 60 women randomly assigned to either vaginal chlorhexidine gluconate (N=30) or oral fluconazole (N=30). Baseline plus 3 follow-up visits (baseline/inclusion, 1 week, 3 months and 6 months) are planned.

***Primary outcome****:* Proportion of women with negative cultures for *Candida albicans* 1week post-treatment.

***Secondary outcomes****:*

- Negative cultures for *Candida albicans* at 3 months’ and 6 months’ follow-ups, after end of prophylactic treatment.
- Analysis of proportion of women with adverse events (AE). The AEs will also be reported in descriptive terms and summarized for each treatment arm.
- Proportion of women with symptom score > 2. Each symptom of typical discharge, itching, dryness of the skin/mucosa, burning and pain will generate 1 point of a composite index (range 0-5).
- Proportion of women with examination score >2. Each finding of redness skin/mucosa, typical discharge, dry skin/mucosa, fissures skin/mucosa, visible candida hyphae in the microscope will generate 1 point of a composite index (range 0-5).
- Proportion of women with reduced vaginal lactobacilli content in vaginal smears measured by a semi-quantitative method as normal or reduced quantity.
- Proportion of women with relapse of *Candida albicans* infection between end of treatment and end of prophylactic treatment (1week post treatment to 3 months’ follow-up) and between 3- and 6 months’ follow-up after end of prophylactic treatment.
- Proportion of women with possible toxic effect on the vaginal epithelium, defined as disruption and/or inflammation of the epithelial lining, analyzed from vaginal biopsies before and after treatment and prophylaxis.
- Further analysis of mucosa inflammatory mechanism and biofilm formation during and after treatment and prophylaxis, analyzed from vaginal biopsies. The methods for these *in vitro* exploratory analyses are not yet decided on.

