***Statistical methods:***

Analysis for differences over time for treatment efficacy, AEs, symptom- and examination score, impact on vaginal lactobacilli and relapses will be analyzed for all randomized patients (i.e. intent-to-treat ITT). Additionally, we will also examine efficacy for the per-protocol (PP) population. Four time points will be used to study the efficacy (proportion of participants with negative cultures for *Candida albicans*) in each treatment arm (baseline, 1w post-treatment, follow-up 3 and 6 months). We will examine the difference in means, proportions and median values using 95% confidence intervals (CI). The CI interval will be computed using 1) for a proportion in one sample and 2) logistic or multinomial logistic regression analysis.

Differences in baseline characteristics between the CHG and FLZ groups will be analyzed with Chi2 for categorical data, Mann Whitney U test for ordinal data, or t-test for continuous data to examine potential selection bias at randomization. Differences in drop-out rates across treatment arms will also be analyzed using Mann Whitney U test.

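### A positive result would exclude only a deficit of about 30 points in culture clearance, which does not support 'at least as effective', and the sentence linking the margin to success is reversed

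*Protocol*

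**What the plan says.** Protocol section 10.4 (Sample size calculations) takes its FLZ rate from an earlier study: "After fluconazole treatment, 14% participants were still culture positive, with 86% success rate of primary outcome". It assumes the same rate for CHG, "success for experimental treatment with CHG in the current study= 86"%, and then sets the limit and size: "with non-inferiority limit= 30%, 46 participants are needed (23 in each group) to achieve a power of 90 % not to exclude an effect-size of 30"%. It closes with "All test will be performed at the 5% significance level", without saying whether the level is one- or two-sided. Section 10.2.1 (Statistical methods) plans the comparison differently: "We will examine the difference in means, proportions and median values using 95% confidence intervals (CI").

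The question is worded more strongly than the limit. Section 10.2.1 states the aim as whether CHG "is at least as effective and safe as oral fluconazole (FLZ) as treatment and prophylaxis for recurrent vulvovaginal candidiasis". The synopsis ties the hoped-for benefits to a result of the same form: "If CHG is at least as effective as FLZ with little impact on vaginal lactobacillus". The primary objective and the overall study design section use the same phrase. The margin appears only in section 10.4, and the protocol gives no clinical or statistical reason for it.

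**The concern.** A non-inferiority result means only what its margin excludes. If the margin is 30 absolute points, success shows that CHG does not clear 30 or more points fewer infections than FLZ. It does not show that CHG clears as many. The protocol offers no argument that a loss approaching 30 points would be acceptable, yet it puts the question throughout as whether CHG is at least as effective.

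The decision sentence adds to this. It promises power "to achieve a power of 90 % not to exclude an effect-size of 30"%. Non-inferiority needs power to exclude a deficit of that size. Read literally, the only sentence joining the margin to success describes the opposite of the intended test.

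At stake is how a positive trial is reported: a result compatible with a sizeable loss of efficacy could be described as showing none.

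**Working it through.** **Inputs.** From section 10.4: FLZ clearance 0.86, CHG clearance 0.86, limit 0.30, power 90%, level 5%. From section 10.2.1: 95% confidence intervals. From the randomization section: 1:1 allocation. Planned size: 30 per arm.

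**Step 1: reproduce the plan's figure.** With an absolute margin and one-sided 5%:

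n per group = (1.645 + 1.2816)² × 2 × 0.86 × 0.14 / 0.30² = 22.9, so 23 per group and 46 in total. This matches.

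- With one-sided 2.5% (a two-sided 95% CI): (1.960 + 1.2816)² × 2 × 0.86 × 0.14 / 0.30² = 28.1, so 29 per group. This does not match.
- With a relative margin (0.30 × 0.86 = 0.258) at one-sided 5%: 8.565 × 0.2408 / 0.258² = 31.0, so 31 per group. This does not match.

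The stated size therefore rests on 30 absolute points and one-sided 5%, which corresponds to a 90% CI. Section 10.2.1 names 95% CIs, so both are shown below.

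**Step 2: the null boundary.** 0.86 − 0.30 = 0.56 clearance on CHG. Failures are 44% against 14%, a ratio of 0.44/0.14 = 3.1.

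**Step 3: how often true losses pass.** All pairs of binomial outcomes were enumerated with FLZ at 0.86 and 30 evaluable per arm. The table gives the probability that the lower limit for CHG minus FLZ lies above −0.30, by the Wald and Newcombe intervals.

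| True CHG clearance | Failures vs 14% | 95% CI (Wald / Newcombe) | 90% CI (Wald / Newcombe) |
|---|---|---|---|
| 79% | 21%, 1.5-fold | 0.66 / 0.65 | 0.76 / 0.77 |
| 76% | 24%, 1.7-fold | 0.52 / 0.52 | 0.63 / 0.66 |
| 72% | 28%, 2-fold | 0.35 / 0.35 | 0.46 / 0.49 |
| 56% (boundary) | 44%, 3.1-fold | 0.027 / 0.029 | 0.050 / 0.057 |

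With 23 evaluable per arm, CHG at 79% still passes about 54% (95% CI) or 66% (90% CI) of the time.

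**Step 4: an observed result that passes.** CHG 23/30 (76.7%) against FLZ 26/30 (86.7%):

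- Difference = −0.100.
- SE = √(0.767 × 0.233/30 + 0.867 × 0.133/30) = 0.0991.
- 95% lower limit = −0.100 − 1.960 × 0.0991 = −0.294, which is above −0.30.

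Non-inferiority would be declared with 7 failures against 4, or 1.75 times as many.

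**The case against.** Five points can be made on the other side.

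- **The boundary is what the test rejects.** A reader might infer that CHG with three times the failures would be accepted. The documents do not support that: CHG at 56% passes only about 3 to 6% of the time. The 3.1-fold ratio describes the boundary and not a typical passing result. This objection stands in full, so the concern rests on the intermediate losses.
- **Any margin lets losses inside it pass part of the time.** The protocol does not define a clinically important loss, so calling 7 or 10 points important would be a reviewer's judgement. This also stands. What remains is the mismatch between what the test excludes and how the question is worded.
- **The phrase is an aim and not a decision rule.** The trial is labelled Phase II and non-inferiority, and the synopsis sentence is conditional on other findings too. This is fair: the protocol does not fix the phrase as the reported conclusion. But no weaker conclusion is stated anywhere, and the Phase II label is not used to explain the margin.
- **The reversed sentence is a slip.** The design label and the reproducible size make the intended direction clear. That is probably right, but the sentence still needs correcting because it is the only link between margin and success.
- **The statistical analysis plan, listed as an attachment, may hold the rule and the reason.** It may, and an omission alone would not carry this point. The protocol itself, however, fixes the margin, words the power statement backwards and states the stronger question.

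**Conclusion.** The concern holds in a limited form. The sample size arithmetic is sound. The margin is 30 absolute points with no reason given in the protocol, and a positive result would exclude only a deficit of about that size. True CHG clearance of 79% would be declared non-inferior about 65% (95% CI) or 76% (90% CI) of the time, and 72% about 35% or 46-49%. Such a result does not support saying that CHG is at least as effective as FLZ. The power sentence states the reverse of the test.

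The figures assume that FLZ truly clears 86%, that all 30 women per arm are evaluable, and that the verdict is read from a Wald or Newcombe interval.

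A reader might also infer that 60 women could carry a clearly tighter margin. The documents do not support this: the increase from 46 to 60 is the drop-out allowance. With a 95% CI and 90% power, the detectable margin is (1.960 + 1.2816) × √(2 × 0.86 × 0.14/30) = 0.29 with 30 per arm, and 0.33 if 30 is replaced by 23.

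**What to change.** 1. In section 10.4, replace the closing clause on power with a rule in the right direction: non-inferiority is concluded if the lower confidence limit for CHG minus FLZ in the proportion culture-negative at 1 week lies above −30 percentage points, so that a 30-point deficit is excluded.
2. Give the clinical or statistical reason for 30 points, or point to it if the statistical analysis plan holds it. Failing that, word the conclusion in the synopsis, the objectives and section 10.2.1 as: not more than 30 percentage points worse in 1-week culture clearance (tolerates 56% if FLZ is 86%). In that case, do not report a positive result as 'at least as effective'.
3. Report the observed difference with its confidence interval alongside the verdict, so that readers can judge it against any tighter limit.

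The cost is a few wording changes and a more modest stated claim. No patients, visits or procedures are added.

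### The 23 per group for 90% power fits only a one-sided 5% test; with the planned 95% confidence interval it gives about 83%, and most of the drop-out allowance goes

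*Protocol*

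**What the plan says.** Section 10.4 (Sample size calculations) lists its inputs as "α= 5% β= 90" percent, "success for routine FLZ treatment= 86" percent and "success for experimental treatment with CHG in the current study= 86" percent, with a non-inferiority limit of 30%. Its result is that "46 participants are needed (23 in each group) to achieve a power of 90 % not to exclude an effect-size of 30" percent. Since the sentence claims 90% power, the beta of 90% is read here as a mislabelled power.

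The section then says "60 participants will be included in case of drop-outs", and closes with "All test will be performed at the 5% significance level". Neither this sentence nor the list of inputs says whether the 5% is one- or two-sided.

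Section 10.2.1 (Statistical methods) says: "We will examine the difference in means, proportions and median values using 95% confidence intervals (CI"). No other interval is planned for a difference in proportions. No section mentions a one-sided test or a 90% interval, or says which confidence limit is compared with the 30-point margin.

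**The concern.** The primary endpoint is a proportion, and non-inferiority is normally read from the lower confidence limit of the difference. The lower limit of a two-sided 95% interval is a one-sided test at 2.5%; that of a two-sided 90% interval is a one-sided test at 5%. Sample size and analysis must use the same one. Here the number of women appears to come from the 5% version, while the only interval planned belongs to the 2.5% version.

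Two things are at stake. First, a reader of section 10.4 would regard 46 evaluable women as enough for 90% power and would not worry about losing up to 14 of 60. Secondly, if the 90% interval excluded a 30-point deficit but the 95% interval did not, the result could be called either way. In an open trial that choice should be fixed before the data are seen.

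**Working it through.** **Inputs** (section 10.4, with the 1:1 ratio from the section on randomization): success 0.86 in each arm, true difference 0, margin 0.30, power 90% (z = 1.2816).

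**Formula** (unpooled normal approximation):

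n per group = 2 × 0.86 × 0.14 × (z_alpha + z_power)² / 0.30² = 0.2408 × (z_alpha + z_power)² / 0.09

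**Step 1: reproduce the protocol's figure.**
- One-sided 5% (z_alpha = 1.645), 90% power: 22.91, so 23 per group (46). This matches.
- One-sided 2.5% (z_alpha = 1.960), 90% power: 28.11, so 29 per group (58). This does not match.
- At 80% power the two levels give 17 and 22 per group, so that does not explain 23 either.

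**Step 2: power at a given number evaluable.**

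Power = Φ(0.30 / √(0.2408 / n) − z_alpha)

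At n = 23 the standard error is √(0.2408 / 23) = 0.1023 and 0.30 / 0.1023 = 2.932. Then Φ(2.932 − 1.645) = 90.1% and Φ(2.932 − 1.960) = 83.4%.

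| Evaluable per group | Total | Lost from 60 | Power, one-sided 5% (90% CI) | Power, one-sided 2.5% (95% CI) |
|---|---|---|---|---|
| 23 | 46 | 14 (23.3%) | 90.1% | 83.4% |
| 25 | 50 | 10 (16.7%) | 92.1% | 86.4% |
| 27 | 54 | 6 (10.0%) | 93.7% | 88.8% |
| 28 | 56 | 4 (6.7%) | 94.4% | 89.9% |
| 29 | 58 | 2 (3.3%) | 95.0% | 90.9% |
| 30 | 60 | 0 | 95.6% | 91.8% |

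Losses are taken as equal in the two arms.

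**Step 3: check by full binomial enumeration.** The protocol names none of these interval methods for the difference, so they serve only as a check.

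| Per group | Level | Wald | Newcombe | Farrington-Manning score |
|---|---|---|---|---|
| 23 | one-sided 5% | 88.8% | 88.9% | 86.6% |
| 23 | one-sided 2.5% | 82.2% | 81.6% | 77.5% |
| 30 | one-sided 2.5% | 91.0% | 90.0% | 88.6% |

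At 23 per group, moving from the 5% to the 2.5% level costs about 7 points with Wald or Newcombe (88.8 − 82.2 = 6.6; 88.9 − 81.6 = 7.3). The approximation gives the same size of loss (90.1 − 83.4 = 6.7). The lower score figure partly reflects the method itself, because that method is already below 90% at the 5% level.

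**The case against.** The arithmetic is not in dispute. The case against concerns what the protocol commits to and how much it matters.

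- **The one-sided 5% is inferred.** It is nowhere written. A reader might infer that the protocol adopts a one-sided 5% test and then contradicts it. The text supports only that the sidedness is unstated and that 23 per group comes back at that level alone. This stands.
- **The 95% interval is not named as the decision rule.** Section 10.2.1 says differences will be examined with it, in a general sentence covering means, proportions and medians. A 95% interval for reporting can coexist with a one-sided 5% test for the decision, and the SAP may fix the limit. This stands in part: it makes the 83% conditional. But it is the only interval planned for a difference in proportions, and no SAP wording can make 23 per group sufficient for 90% power under a 95% limit.
- **The trial is barely affected at full size.** A reader might infer that it is underpowered. With all 60 evaluable it is not: power is about 92%, or 90–91% by enumeration with Wald or Newcombe. The 83% needs a loss of 14 women before the primary culture, which is taken early, at Visit 3, and the main analysis is by intention to treat. This stands.
- **Power declines gradually.** Losing four women leaves 89.9%, so it would be too strict to say that only two can be lost. This stands, and is why the allowance is given as a range.

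One point runs the other way. Efficacy is also examined per protocol, and the list of abbreviations restricts that set to women who complete the study without deviations. It could fall below 56 to 58 women more easily than the number with a Visit 3 culture.

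**Conclusion.** The concern holds as a mismatch between the stated power and the only planned interval, and is of moderate weight. The 46 women for 90% power are correct for a one-sided 5% test. If instead the lower limit of a two-sided 95% interval decides non-inferiority, 46 evaluable women give about 83% power (about 82% by enumeration with Wald or Newcombe). The chance of missing non-inferiority when the arms are truly equal is then about 17% rather than 10%.

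By the same approximation, 90% power needs 29 evaluable per group. The loss that 60 randomised women can absorb is therefore about 3% (58 evaluable) to 7% (56 evaluable, 89.9%), not 23%.

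This rests on three assumptions: the 95% interval is two-sided, its lower limit is the deciding one, and success is 86% in both arms. The documents do not show that the planned 60 are too few, or that a one-sided 5% test has been formally chosen.

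**What to change.** State in section 10.4 whether alpha is one- or two-sided and which confidence limit is compared with the 30-point margin. Then choose one of two routes:

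1. **Keep the 95% interval.** Restate the requirement as 29 evaluable women per group (58) for 90% power by the normal approximation. Add that 60 randomised allows about 3% loss, and that power is about 83% if only 23 per group are evaluable. Name the approximation, because the figure depends on the method: enumeration at 29 per group gives 90.3% with Wald and 89.1% with Newcombe.
2. **Keep 23 per group.** Declare and justify a one-sided 5% test in section 10.4, and plan a 90% interval for the primary comparison in section 10.2.1.

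The SAP should carry the same rule. Either route costs wording only and needs no added recruitment. The first makes the power statement less favourable; the second accepts a more lenient test.

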## Interim analysis (if relevant)

No interim analysis will be performed.

# Quality Control and Quality Assurance

The sponsor is responsible for planning the Quality Control and Assurance with regular monitoring. An independent monitor has been assigned and will perform the monitoring as describe 11.2.

## Quality Assurance and Sponsor oversight

The clinical trial will be performed at the research department at the Department of OB&GYN, Danderyd Hospital. The sponsor has the responsibility for the monitoring plan and to assure direct access to all source data for monitoring, audits and inspections.

Only 3 personnel will be involved in the study; the principal- and co-investigator together with the research coordinator. The study personnel have long experience of working together and have planned the study in close co-operation. No special training of personnel is needed.

The study coordinator role is to book the appointments for the participants, collect data from vaginal cultures and other laboratory tests, handle the CRFs and be of help during monitoring and audits. Any AEs can directly be reported to the study coordinator and further reported to the investigators and sponsor if needed.

The principal (=sponsor) and co-investigator will conduct the study visits, give the oral and written information and collect the signed consents, check the inclusion- and exclusion criteria and decide on the final inclusion of the participants.

The major risk of the study has been identified to be correlated to the study drug fluconazole which serves as the reference treatment in the trial. Fluconazole is an approved medication and caution to avoid known AEs has been taken in the inclusion- and exclusion criteria in the protocol. No serious AEs with Hibitane is expected. Any AEs can be reported directly to the study coordinator or by the use of the electronic weekly dairy.

